We have based our sample size calculation on our preliminary study. We plan to enroll and randomize 140 participants (2:2:1) to ILM, SILM, and WLC. Assuming a 20% attrition rate, we will have 45 participants in each of the ILM and SILM groups and 22 participants in the WLC group who will provide evaluable outcomes. In our previous study, we found that ILM produced a greater reduction in BFI-C intensity at the end of intervention (Week 4 from baseline) at a magnitude of 0.60 SD (Standard Deviation) as compared to SILM. Given an alpha of 5%, with 45 subjects in each of the ILM and SILM groups, we will be able to detect a between-group difference of reduction in BFI-C of 0.60 SD with 80% power. With 45 subjects each in the ILM and SILM groups and 22 participants in the WLC group, a power of 80% and two-sided alpha of 0.05, we will be able to detect an effect size of 0.71 SD (i.e., difference of reduction in BFI-C) between ILM and WLC or SILM and WLC groups. This is a conservative way to estimate sample size since the longitudinal analysis using all repeated measures with the mixed-effects model specified in the analysis plan will provide higher power than a *t* test.

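### The 0.71 SD stated as detectable in the waitlist comparisons does not follow from 45 vs 22 evaluable participants, which give 0.74 SD (minor correction)

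*Protocol article*

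**What the plan says.** All the inputs are in section 3.15 (Statistical analysis and sample size calculation) of the protocol article.

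- Enrolment: "We plan to enroll and randomize 140 participants (2:2:1) to ILM, SILM, and WLC".
- Evaluable numbers: "Assuming a 20% attrition rate", the article expects that "we will have 45 participants in each of the ILM and SILM groups and 22 participants in the WLC group" will provide outcomes.
- ILM vs SILM, at 5% alpha: "we will be able to detect a between-group difference of reduction in BFI-C of 0.60 SD with 80% power".
- Waitlist comparisons, with the same evaluable numbers, 80% power and a two-sided 5% level, carry this claim: "we will be able to detect an effect size of 0.71 SD (i.e., difference of reduction in BFI-C) between ILM and WLC", and likewise for SILM vs WLC.
- Method: "This is a conservative way to estimate sample size since the longitudinal analysis using all repeated measures" in the planned mixed-effects model is expected to be more powerful than a t test. The 0.60 and 0.71 SD figures are therefore t-test figures, before any gain from repeated measures.

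Section 2 (Specific aims and hypotheses) puts ILM against both SILM and WLC in the primary hypothesis. SILM vs WLC is not part of it.

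**The concern.** The two detectable differences share a method, an alpha and a power, and differ only in the size of the comparison group. Cutting that group from 45 to 22 raises the standard error of the difference by a known factor, so the second figure can be checked against the first. Scaling 0.60 SD by that factor gives about 0.74 SD, which suggests that 0.71 SD was computed from other group sizes or mis-stated.

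What is at stake is limited. ILM vs WLC belongs to the primary hypothesis, and the Discussion says the usual-care group was added to estimate the overall effect of treatment. The stated sensitivity of that comparison should therefore match the stated numbers. The figure does not drive the sample size.

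**Working it through.** **Inputs (all from section 3.15).** 140 randomised 2:2:1 is 56, 56 and 28. With 20% attrition, 56 × 0.8 = 44.8 and 28 × 0.8 = 22.4, which the article gives as 45, 45 and 22. Two-sided alpha is 0.05, power 80%, and the sizing test is a two-sample t test. Effects are in SD units.

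**Formulas.** For a difference d, the noncentrality is d / √(1/n₁ + 1/n₂) with n₁ + n₂ − 2 degrees of freedom. The detectable d is the value at which the noncentral t distribution gives 80% power. The normal approximation is d = (1.960 + 0.842) × √(1/n₁ + 1/n₂).

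**Step 1: the companion figure, 45 vs 45.**
- √(1/45 + 1/45) = 0.2108, with 88 degrees of freedom.
- t test: detectable 0.597 SD; power at 0.60 SD is 80.4%.
- Normal approximation: 2.802 × 0.2108 = 0.591 SD.

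The stated 0.60 SD reproduces, which confirms the method.

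**Step 2: the waitlist figure, 45 vs 22.**
- √(1/45 + 1/22) = √0.06768 = 0.2601, with 65 degrees of freedom.
- t test: detectable 0.740 SD; power at 0.71 SD is 76.7%.
- Normal approximation: 2.802 × 0.2601 = 0.729 SD. At 0.71 SD, 0.71 / 0.2601 = 2.729, and 2.729 − 1.960 = 0.769, which gives 77.9% power.

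The stated 0.71 SD does not reproduce by either route. Scaling from step 1 agrees: 0.597 × 0.2601 / 0.2108 = 0.737 SD, before the small loss of degrees of freedom.

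**Step 3: could another reading give 0.71 SD?**

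| Reading | Detectable at 80% power (t test unless noted) |
|---|---|
| Unrounded, 44.8 vs 22.4 | 0.736 SD |
| 45 vs 22, error df pooled over three arms (109) | 0.735 SD (77.2% power at 0.71 SD) |
| 45 vs 23 | 0.729 SD |
| 45 vs 22, one-sided alpha | 0.654 SD |
| No attrition, 56 vs 28 | 0.656 SD |
| 45 vs 22, alpha 0.025 or 0.0167 | 0.82 or 0.86 SD |
| 45 vs 24, normal approximation | 0.708 SD |
| 45 vs 25 | 0.709 SD (80.1% power at 0.71 SD) |
| 48 vs 24 | 0.710 SD |
| Attrition on the waitlist only, 56 vs 22 | 0.714 SD (0.705 by normal approximation) |

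Only the last four rows come near 0.71 SD, and each uses group sizes the article does not give for this comparison.

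**The case against.** The strongest reply is that the gap is trivial and that the planned analysis may close it. A mixed model using repeated measures can be more precise than a t test on change. As an illustration under an assumption the article does not make: moving from 0.740 to 0.71 SD needs the residual variance to fall to (0.71 / 0.740)² = 0.92 of its value, a reduction of about 8%, equivalent to a covariate correlation of about 0.28. That is a modest requirement. This part of the reply stands, and the general remark about the mixed model is reasonable. It does not rescue the figure, because 0.71 SD is offered before any such gain and no correlation is given to quantify one.

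It is also fair that the sample size rests on ILM vs SILM, where the calculation is sound. The waitlist figure only describes what the chosen numbers can detect.

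Three stronger inferences are tempting, and the article does not support them:

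- **That the claim of conservatism is false and should go.** That sentence gives its own reason, which concerns sizing by t test when a mixed model is planned. A slip in one output does not make it untrue.
- **That the waitlist comparison is badly underpowered.** Power for 45 vs 22 at 0.60 SD is indeed 62%. But 0.60 SD is the real-vs-sham effect from the preliminary study, and the article never assumes it for the waitlist comparison.
- **That a null ILM vs WLC result would be misread.** Such a result is read mainly from its estimate and confidence interval, and a shift of 0.03 SD in the planned detectable difference would rarely change that reading.

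**Conclusion.** The waitlist figure is wrong as written, and the error is minor. On the stated inputs the detectable difference is 0.74 SD rather than 0.71 SD (0.73 SD by the normal approximation), and power at 0.71 SD is about 77% rather than 80% (78% by the normal approximation). This applies equally to ILM vs WLC and SILM vs WLC, which have the same group sizes. It rests on the two-sample t test that the article names as its basis, equal SDs in the two groups, and the evaluable numbers as printed. The ILM vs SILM calculation, the enrolment target and the planned analysis are unaffected.

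**What to change.** In section 3.15, restate the waitlist sentence along these lines: with 45 and 22 evaluable participants and two-sided alpha 0.05, there is 80% power to detect 0.74 SD (77% power for 0.71 SD) for ILM vs WLC or SILM vs WLC. If 0.71 SD was computed from other evaluable numbers, state those instead; by t test it needs about 25 evaluable waitlist participants against 45.

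The sentence on the mixed model may stay as a general remark. If it is meant to support 0.71 SD, the assumed correlation and the resulting power should be given.

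The cost is one sentence and a slightly less favourable figure, with no change to enrolment or analysis.

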### Ethics and dissemination

3.16

This trial will be conducted in accordance with the latest revision of the *Declaration of Helsinki* governing standards for good clinical practice. Patient confidentiality will be guaranteed because the data will be de-identified. The results of the clinical trial will be published independently and transparently, regardless of the results.

## Discussion

4

Cancer-related fatigue is the most common and debilitating symptom experienced by many cancer survivors. CRF often co-occurs with other symptoms such as pain, sleep disturbances, anxiety, and depression that follow a similar time course in relation to cancer or its treatment. NCCN clinical guidelines put a major emphasis on the various aspects of the prevention and treatment of CRF, including management of comorbidities (e.g., pain, insomnia, anxiety, and depression).^[29]^ In particular, some research has shown a significant link between fatigue, joint pain, and insomnia in breast cancer patients.^[45,46]^ In addition, there is growing evidence of acupuncture's impact on cancer survivors with fatigue, anxiety, depression, insomnia, and pain.^[17,18]^ In our preliminary study, infrared laser moxibustion appeared to be safe and efficacious for improving CRF.^[25]^ Hence, we conduct this trial to confirm that infrared laser moxibustion will both reduce fatigue and result in greater improvement in co-morbidities.

Telomeres cap the ends of linear chromosomes and play a role in maintaining genomic stability. Telomere length (TL) is increasingly being examined as a biomarker of accumulated cellular damage and human aging, and is associated with quality of life in cancer patients.^[47]^ Telomere shortening occurs via normal aging, but can be accelerated through exposure to oxidative stress, which plays a major role in the pathophysiology of several chronic inflammatory diseases.^[48,49]^ Immune cell telomere shortness is linked to many chronic disease states and earlier mortality. TL, which may be regarded as a susceptible biomarker of psychosocial influences (particularly stress), and is associated with fatigue.^[50,51]^ TL shortening can be caused by stress, while a decompression intervention can affect TL in cancer patients.^[52–54]^ Therefore, it is hypothesized that telomere length reduces at a faster rate during periods of stress and, therefore, assessment of TL might be a useful biomarker in the progression of CRF.

The strengths of this study come from our combination of rigorous study design and a novel noninvasive and painless moxibustion therapy. To our knowledge, this is the first trial to evaluate the definitive efficacy of infrared laser moxibustion and its durable treatment of CRF in survivors of breast cancer. Outcome expectancy has long been considered an important predictor of treatment outcomes and has gained important consideration in acupuncture research in recent years.^[55]^ The AES has also been validated in breast cancer survivors and is sensitive to change over time in response to acupuncture treatment.^[56]^ This trial is the first to assess response expectancy of laser moxibustion to fatigue among breast cancer survivors. We will be able to explore how pre-treatment expectancy influence therapeutic response in real and sham laser moxibustion interventions. Findings from subjective data (various questionnaires) and objective data (e.g., telomere length) will enhance our understanding of the overall treatment effect and mechanisms of ILM.

Despite the novelty and strengths of this trial, it is not without limitations. First, it is a partial double-blind trial since we include a waitlist control group. Our previous randomized, double-blind, placebo-controlled pilot trial preliminarily demonstrated the efficacy of infrared laser moxibustion in CRF. In this trial, we have added a usual care group to estimate the overall effect of laser moxibustion for CRF. In addition, this study is conducted in China so its generalizability beyond the Chinese population is unknown. If the findings of this trial are positive, we then plan to conduct a follow-up study in populations outside of China.

Despite these limitations, this trial will enhance our understanding of the specific efficacy and overall treatment effect of ILM for cancer-related fatigue and co-morbid symptoms. The results of our study have the potential to improve symptom control and quality of life for millions of breast cancer survivors worldwide.
